### Data collection, analysis and management

**
*Quantitative data collection.*
** Five key outcomes will be assessed prospectively, via JISC online survey (
www.onlinesurveys.ac.uk) at four time-points – before commencement of the intervention, mid-way through the intervention, on completion of the intervention and one-month post-completion. (
Table 2). This will allow examination of preliminary evidence for changes in outcomes collected by questionnaire over the course of the intervention, as well as questionnaire completion rates to inform the design of a future evaluation. As we are most interested in changes in outcomes that are sustained beyond intervention delivery, our main exploratory analysis will focus on the change in outcomes pre-intervention versus 4 weeks post intervention. This data will help us identify key outcomes and sample size needed for a future evaluation

**Table 2. T2:** Schedule of enrolment, interventions, and assessments.

WEEK	Pre-intervention	Wk1	Wk2	Wk3	Wk4	Wk5	Wk6	Wk7	Wk8	Wk9	Wk10	Wk11	Wk12	Wk13-16
**EVALUATION** **TIMEPOINTS**	**t0**			**t1**				**t2**					**t3**	
**ENROLMENT**														
Study promotion	X													
Informed consent	X													
Technology support session	X													
**INTERVENTION**		Introduction	Values	Awareness	Review	Openess	Diffusion	Compassion	Review					
Virutal classroom modules		X			X				X					
E-Learning module			X	X		X	X	X						
**QUANTITATIVE** **OUTCOMES**														
Perceived stress	X			X				X					X	
Professional Quality of Life	X			X				X					X	
Mental wellbeing	X			X				X					X	
Mindful Healthcare	X			X				X					X	
Psychological flexibility	X			X				X					X	
Feasibility data collection										X				X
**QUALITATIVE** **DATA**														X
Focus groups														X
Interviews														X

**
*Self-reported, perceived stress*
** will be assessed by the Perceived Stress Scale (PSS)
^
29,
30
^. This scale assesses participants' appraisals of stressful situations, including perceptions of how unpredictable, uncontrollable, and overloaded their lives have been over a defined period. We will use the 10-item scale consisting of a Perceived Helplessness subscale (6-items) and a Perceived self-efficacy subscale (4-items)
^
30
^.

**
*Workplace quality of life*
** will be assessed by the Professional Quality of Life scale (ProQol)
^
31
^. The ProQOL consists of 30 items in three subscales (10 items per subscale) designed to measure
*compassion*
*satisfaction (pleasured derived from doing your work well)*,
*burnout* and
*secondary trauma*. Each item rates the frequency of an experience on a scale from 0 (never) to 5 (very often).

**
*Wellbeing*
** will be assessed using the Edinburgh Warwick Mental Wellbeing Scale
^
32,
33
^. This is a 14-item scale, covering both hedonic and eudemonic aspects of mental health including positive affect, satisfying interpersonal relationships and positive functioning. Higher scores reflect increased wellbeing.

**
*Healthcare professional experience*
** will be assessed by the Mindful Healthcare Scale which assesses engagement, awareness and defusion – 13 items. This measure is being developed at the University of Edinburgh
^
3,
34
^.

**
*Psychological flexibility*
** will be assessed by the CompACT.
^
35
^ It consists of 23 items over 3 sub-scales -
*openness to experience*,
*behavioural awareness*,
*and valued action*. Participants are asked to rate the degree to which a statement is true for them using a 7-point scale. The higher the score, the higher participant's level of psychological flexibility.

**Feasibility outcomes** will be assessed retrospectively via routine data collection on completion of the intervention and qualitative data collection. Data will include:

the number of participants recruited (target is 24 – 30 participants),the number of participants who complete the intervention, i.e. participant attended the final session or reported they had completed at least 6 of 8 modules (target is two-thirds of those who completed the intervention)the number of participants who complete the outcome measures (target is at least two-thirds of those who commence the intervention).The number of participants who take part in post-intervention focus groups or interviews (target is 50–75% of those recruited, given that focus groups will be run during work time and some participants will be unable to take part due to work schedules and annual leave).

We will also explore stress levels at baseline to determine whether those with moderate to high levels of stress were recruited and examine any potential links between baseline stress and participant retention.

**
*Qualitative data collection.*
** We will conduct virtual focus groups with participants one month following completion of the intervention to explore their experience of ACT training; views on what elements were most and least useful; perception of any changes in how they manage challenging situations; and whether/in what way skills learnt during the training might improve the care they provide to patients and families. All participants will be invited to take part. Focus groups will be run via MS Teams, recorded, and transcribed for analysis. Qualitative data will be collected by an experienced qualitative researcher (BS), based at a different institution to participants, and not personally known to participants prior to data collection. Participants who drop-out will be invited to share their reasons via brief interview. With permission, the interview will take place via MS Teams, and will be recorded and transcribed. Where participants drop-out and choose not to take part in an interview, we will ask permission to note their main reason(s) for drop-out.

**
*Quantitative and qualitative data analysis.*
** The main quantitative outcomes of interest are feasibility outcomes which will include rates of participant recruitment and retention over the course of the study. As this is a feasibility trial, it is likely to be underpowered to detect statistically significant improvements in the non-feasibility outcomes (e.g. stress, quality of life, wellbeing) and so these will be reported descriptively (mean, standard deviation, range etc.). Instead, the outcome data collected will help ascertain whether there is any preliminary evidence for intervention effectiveness. It will be also used to estimate effect sizes and determine sample sizes for a future full-scale evaluation. Any missing data will be handled using pairwise deletion methods. We are most interested in any evidence for improvements in outcomes between pre-intervention baseline (T0) and post-intervention follow-up (T3). Data will be analysed in IBM SPSS Statistics, V24. Qualitative data analysis will be guided by the framework approach using NVivo 12
^
36
^ and will provide vital insights on intervention acceptability, perceived effectiveness and recommendations for further refinement.

**
*Stakeholder workshop to cross-validate emergent findings, refine the intervention and identify considerations for future full scale evaluation and implementation.*
** A stakeholder workshop will be organised, bringing together participants, members of the research team, staff managers and those who would be involved in intervention delivery if it were implemented, to discuss findings. At this workshop participants will have the opportunity to highlight themes that resonate with them, as well as those that do not, and identify anything that may have been missed. We will review feasibility data and seek feedback on how the intervention could be further refined to meet the needs of palliative care staff in the organisational context in which the intervention would be implemented. We will explore costs and resource use from multiple perspectives and consider short and long terms outcomes for consideration in a future full-scale evaluation. 

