*4*	** *Review of materials* **	**90 minutes**	Review, troubleshooting, clarifying materials. Discussion.	Synchronous online virtual classroom Led by an ACT trainer (DG)
*5*	** *Openness* **	30 minutes	Developing self-awareness, becoming more open, making room.	Self-directed, asynchronous materials Group chat Homework
*6*	** *Defusion* **	30 minutes	Unhooking from difficult thoughts and feelings	Self-directed, asynchronous materials Group chat Homework
**7**	**Compassion**	30 minutes	Kindness to self and others	Self-directed, asynchronous materials Group chat Homework
**8**	**Review and** **trouble shooting**	**90 minutes**	Review, troubleshooting, clarifying materials. Discussion.	Synchronous online virtual classroom Led by an ACT trainer (DG)

**
*Format.*
** There will be 8 modules delivered via MS Teams over an 8-week period (
Table 1). Delivery will be via three synchronous virtual classroom sessions and five asynchronous, self-directed, e-learning modules. The three virtual classroom modules will be interactive expert-led sessions. The five self-directed e-learning modules will consist of online reading materials, pre-recorded videos, and reflective exercises. Participants will be encouraged to share experiences with each other and ask questions or seek clarification via the online chat function within MS Teams. Participants will be provided with a workbook (hard-copy) outlining the content for each week alongside related exercises. The workbook can be accessed here:
https://doi.org/10.1186/ISRCTN14313559

**
*Homework.*
** Participants will be asked to complete ‘homework’ each week to reflect on the material and how it relates to themselves and their work. Homework will be brief and non-obligatory but encouraged. Examples of homework would include practicing brief mindfulness exercises or exercises to enhance compassionate responses. Homework will be described in the workbook. 

**
*Adherence*
** To facilitate adherence, participants will also be sent a weekly reminder to alert them when new content is made available. To facilitate engagement, participants will be encouraged to share their experiences of the intervention, and any questions they might have via the online chat function (within MS Teams). 

**
*Benefits of participation.*

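### The completion definition treats attending the last review session as equivalent to doing 6 of 8 modules, so the completion count can overstate how many staff completed the programme, and its target is circular

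*Protocol article*

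**What the plan says.** The protocol article describes the intervention under Intervention design and content (Format and Table 1): "There will be 8 modules delivered via MS Teams over an 8-week period". "Delivery will be via three synchronous virtual classroom sessions and five asynchronous, self-directed, e-learning modules". Table 1 gives 90 minutes to each classroom session (weeks 1, 4 and 8) and 30 minutes to each e-learning module (weeks 2, 3, 5, 6 and 7). The e-learning modules carry the content on values, awareness, openness, defusion and compassion. Week 8 is a review and discussion session.

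Under Data collection, analysis and management, the feasibility outcomes "will be assessed retrospectively via routine data collection on completion of the intervention", together with qualitative data. One of them is the number who complete the intervention, meaning that the participant "attended the final session or reported they had completed at least 6 of 8 modules". Its target is printed as "target is two-thirds of those who completed the intervention". The next item, completion of the outcome measures, has a different denominator: "target is at least two-thirds of those who commence the intervention". The analysis paragraph makes the feasibility outcomes, including recruitment and retention rates, the main quantitative outcomes.

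**The concern.** The two criteria are joined by *or*, and no minimum number of modules is attached to the first. On the plain wording, someone who did none of modules 1 to 7 but joined the week 8 session has completed the intervention. No other part of the article adds a minimum.

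The article thus sets three quarters of the modules as one standard of completion and waives it for anyone present in the last week. The resulting figure mixes staff who worked through the programme with staff who came to its last meeting. That matters because the first research question is whether the online intervention is feasible for these staff. Most of the modules are self-directed, so taking part in the classroom sessions says little about whether the rest was done.

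The target has a separate fault. It measures completers against completers, so it cannot tell a workable format from an unworkable one.

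**Working it through.** **Exposure under each route** (module counts from Format, minutes from Table 1)

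- Whole programme: 3 × 90 + 5 × 30 = 270 + 150 = 420 minutes.
- Final session only: 1/8 = 12.5% of modules; 90/420 = 21% of minutes; 0 of 5 e-learning modules.
- Six of eight modules: 75% of modules. The least time is five e-learning modules and one classroom session, 5 × 30 + 90 = 240 minutes (57%). The most is three of each, 3 × 30 + 3 × 90 = 360 minutes (86%).

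The second route therefore asks for 240/90 = 2.7 to 360/90 = 4 times the minutes that suffice for the first.

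**Effect of *or* on the count.** Let *p* be the share with at least six modules and *f* the share who attend week 8 with fewer than six. The 6-of-8 rule alone gives a completion rate of *p*; the printed rule gives *p* + *f*. The direction is fixed, since *f* cannot be negative. The documents give no value for *f*, and it is zero if every week 8 attender did at least six modules.

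**The target as printed.** Completers divided by completers = 100%, which exceeds two-thirds whenever anyone completes. On this wording the *or* cannot change whether the target is met.

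**Illustration under assumptions that are not in the documents.** Assume that the denominator is those who commence, and that all 24 to 30 recruits commence. Two-thirds is then 24 × 2/3 = 16 or 30 × 2/3 = 20. The probability of meeting the target is P(X ≥ 16) with X ~ Binomial(24, *p* + *f*), or P(X ≥ 20) with X ~ Binomial(30, *p* + *f*). The values of *p* and *f* are assumed.

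| *p* | *f* | n = 24 | n = 30 |
|---|---|---|---|
| 0.50 | 0 | 0.08 | 0.05 |
| 0.50 | 0.10 | 0.33 | 0.29 |
| 0.50 | 0.20 | 0.73 | 0.73 |
| 0.55 | 0 | 0.17 | 0.14 |
| 0.55 | 0.05 | 0.33 | 0.29 |
| 0.55 | 0.10 | 0.53 | 0.51 |
| 0.55 | 0.20 | 0.88 | 0.89 |
| 0.60 | 0 | 0.33 | 0.29 |
| 0.60 | 0.10 | 0.73 | 0.73 |
| 0.60 | 0.20 | 0.96 | 0.97 |

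The rows with *f* = 0 show the 6-of-8 rule alone. The table shows that a modest *f* could decide whether a repaired target is met. It does not show that this will happen.

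**The case against.** The strongest reply is that being present at the last session is a fair sign of still being in the programme at its end. As a marker of retention the first route is reasonable. That stands: the weakness lies in calling it completion, not in recording it.

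A reader might infer that the rule does inflate the result, and that the result is the trial's main retention outcome. The documents support neither. The excess is unknown and may be zero. The article names retention rates among its main outcomes but does not label this count as the retention measure, although it is the only listed item about staying in the intervention.

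It can also be said that the completion figure does not carry the feasibility judgement alone. Outcome-measure completion, focus groups, drop-out interviews and the stakeholder workshop all contribute, and the article ties no stop or go decision to this number. That also stands, and it lowers the severity.

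Reliance on participants' own reports is only partly open to criticism. Five of the eight modules are asynchronous, so some self-report is hard to avoid, and nothing says that classroom attendance will go unrecorded.

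Finally, no passage establishes 6 of 8 as the required exposure. It is, however, the only exposure threshold that the article sets.

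**Conclusion.** The point holds in a limited form. The definition equates two exposures that differ at least 2.7-fold in minutes at the extreme, and the completion count can overstate completion of the eight-module programme by exactly the share who attend week 8 with fewer than six modules. That share cannot be estimated from the documents. A claim that the target would be met under one rule and missed under the other needs assumed counts and an assumed denominator, because the printed target is met by construction.

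The circular denominator is the plainer error and has to be repaired first. Reading it as those who commence is an inference from the neighbouring target, not something the article states. The severity is should-fix: the repair changes what the completion rate can show, but the study's feasibility conclusion draws on other evidence as well.

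**What to change.** 1. Define completion as at least 6 of 8 modules.
2. Report final-session attendance separately, as a retention measure.
3. Show the distribution of modules completed, from 0 to 8, so that readers can apply another threshold.
4. Use observed attendance for the three classroom sessions where it is available, and self-report for the five e-learning modules.
5. Restate the target as two-thirds of those who commence the intervention, in line with the neighbouring target.

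The cost is small: a rewording, and tabulating the two routes apart. The downside is that the completion rate can only stay the same or fall. Study status says that data collection was already under way, so a new weekly question on module completion is not proposed. It would come too late for the weeks already delivered and would itself be self-report. The change of definition should be dated, made before the completion data are examined if that is still possible, and communicated through the route that the article gives for amendments.

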### Participants and sample size

Participants will be recruited from two Marie Curie hospices and from the Marie Curie Nursing Service (Scotland). We will seek a sample size of approximately 30 participants. As this is a feasibility study, sample size has not been formally calculated. Our target sample size is based on prior experience, resources available and the format of the intervention. 

**
*Inclusion criteria.*
** The intervention will be offered to health and social care professionals providing direct support to patients and families, including nursing and medical staff, allied health professionals, social workers, and healthcare assistants. 

**
*Exclusion criteria.*
** Staff who have previously undertaken Acceptance and Commitment Therapy training will be excluded.

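### The intervention-completion target uses completers as its own denominator, so it is met at any level of drop-out and cannot serve as a retention criterion

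*Protocol article*

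**What the plan says.** In the protocol article, under Data collection, analysis and management, the feasibility outcomes are listed with a target for each.

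- Recruitment: "the number of participants recruited (target is 24 – 30 participants").
- Completion of the intervention: "the number of participants who complete the intervention, i.e. participant attended the final session or reported they had completed at least 6 of 8 modules". The target attached to it is "target is two-thirds of those who completed the intervention".
- Completion of the outcome measures: "target is at least two-thirds of those who commence the intervention".
- Focus groups or interviews: "target is 50–75% of those recruited".

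The analysis paragraph that follows gives these outcomes their weight: "The main quantitative outcomes of interest are feasibility outcomes which will include rates of participant recruitment and retention over the course of the study". The section on participants and sample size adds "As this is a feasibility study, sample size has not been formally calculated", so no power or precision calculation lies behind the targets. Under Study status, data collection is described as in progress, to finish in December 2021, with analysis in January 2022.

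**The concern.** A feasibility target is useful only if some plausible result would miss it. The completion target compares the number of completers with a fraction of that same number. Low completion shrinks both sides together, so the comparison carries no information about how many people dropped out.

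This matters because it is the only target in the list that addresses whether participants complete the intervention. The next target can fail, but it concerns return of questionnaires. The last concerns uptake of focus groups and interviews. As written, then, retention in the intervention, a main quantitative outcome, has no threshold that it could fall short of.

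**Working it through.** **Inputs.** Let C be the number of completers and N the number who commence. The article gives no value for N. I take N = 24 and N = 30 from the recruitment target, which assumes that everyone recruited also starts. I read the two-thirds as a minimum, as the next item in the list states explicitly.

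**Figure to reproduce.** There is none. The target is not derived from a sample size calculation, so the check is of its logic.

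**Step 1: the target as written.** The condition is C ≥ (2/3) × C. The ratio is C / C = 1 for every C ≥ 1. At C = 0 the ratio is undefined, and the count form (0 ≥ 0) still holds. With 30 starters:

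| Completers C | Needed as written, (2/3) × C | Met as written? | Share of starters, C / 30 |
|---|---|---|---|
| 1 | 0.67 | yes | 3.3% |
| 5 | 3.33 | yes | 16.7% |
| 10 | 6.67 | yes | 33.3% |
| 19 | 12.67 | yes | 63.3% |
| 20 | 13.33 | yes | 66.7% |

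No value of C misses the target.

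**Step 2: the same fraction with starters as the base.** The condition becomes C ≥ (2/3) × N.

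- N = 24: (2/3) × 24 = 16. So 16/24 = 66.7% passes and 15/24 = 62.5% fails.
- N = 30: (2/3) × 30 = 20. So 20/30 = 66.7% passes and 19/30 = 63.3% fails.
- Five completers of 30 give 5/30 = 17%, which fails.

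**Step 3: does the corrected target discriminate?** With C binomial (N, p), the chance of meeting it is P(C ≥ 16) for N = 24 and P(C ≥ 20) for N = 30. The true completion rates p are illustrative and do not come from the article.

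| True completion rate p | N = 24 | N = 30 |
|---|---|---|
| 50% | 0.08 | 0.05 |
| 60% | 0.33 | 0.29 |
| 75% | 0.88 | 0.89 |
| 80% | 0.96 | 0.97 |

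The corrected target usually fails when completion is poor and usually passes when it is good. The target as written passes in every row.

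**Step 4: does the choice of base matter?** Suppose, for illustration, that 30 are recruited, 24 start and 16 complete. Against starters, 16/24 = 67% meets two-thirds. Against those recruited, 16/30 = 53% does not. The intended base therefore has to be stated and cannot be left to the reader.

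**The case against.** The strongest reply is that this is a slip of the pen and not a flaw of design. The next item has the same fraction with a sensible base, and most readers would mentally substitute starters. That is probably right, and I see no reason to suspect intent. It does not remove the error. The neighbouring items use two different bases, those who commence and those recruited, so they show that the wording is wrong without settling what was meant.

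The second reply is that drop-out will still be seen, and this stands. The outcome itself is a count, the number recruited is also an outcome, and the analysis paragraph commits to "feasibility outcomes which will include rates of participant recruitment and retention over the course of the study". Those who drop out are also invited to give their reasons. A reader might infer that the study as a whole could not reveal poor retention, or that a completion figure of 100% would be published. The documents support neither: five completers of 30 recruited would be visible as exactly that.

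Third, the article states no stop or go rule. Feasibility is judged by mixed methods and discussed at a stakeholder workshop, so no single decision turns on this threshold. That also stands, and it limits the consequence.

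A reader might go further and object that the listed targets do not share one base. That is not an error. Focus group or interview uptake is a separate outcome from retention, everyone is invited, and a base of all recruited suits it. Only the base for completion is defective.

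**Conclusion.** The target is wrong as written. It is met whatever the number of completers, and so cannot act as a criterion for retention in the intervention. That conclusion follows from the wording alone and needs no assumption.

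The defect is limited to this one threshold. It does not hide the data, and no progression rule depends on it. It still deserves correction, because it is the only prespecified target for completing the intervention and it belongs to a main outcome.

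The size of the change, a requirement of 16 of 24 or 20 of 30, rests on two assumptions: that those who commence is the intended base, and that 24 to 30 people commence.

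**What to change.** In the feasibility outcomes list, reword the completion target to use the fraction and base of the item that follows it: "target is at least two-thirds of those who commence the intervention". If those recruited were meant, say so explicitly instead. Either choice makes the target capable of failing.

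Because data collection is already in progress, record the change as a dated amendment through the route set out under Protocol registration and amendments, before the analysis begins. The base is then fixed before the completion figures are assessed.

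The cost is one phrase and an amendment notice. No data collection, sample size or analysis changes. The wording of the registry entry is not available here, so the investigators should check whether it carries the same phrase.

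Reporting completion against both starters and all recruited, or adding confidence intervals, would be a reasonable courtesy to readers. It is a preference and not part of this correction.
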